#### Assessment of quality of life – 8 dimensions multi-attribute utility instrument (AQoL-8D)

The AQoL-8D is a Multi-Attribute Utility (MAU) instrument which will be used to assess health state utility at baseline, immediately following the supervised phase, and at 3, 6 and 12 months [111]. The AQoL-8D contains 35 items which load onto eight dimensions. Three of these dimensions are related to a physical ‘super-dimension’ and the remaining five to a psychosocial (‘mental’) super-dimension [111]. The AQoL-8D has been found to be valid and have good reliability compared to other multi-attribute utility instruments and is particularly suitable when evaluating economic outcomes where psychosocial elements of health are of importance [112].

#### Adverse and serious adverse events

To assess the efficacy of the intervention, adverse events will be recorded by the research team immediately upon their notification. An adverse event will be defined as ‘any untoward medical occurrence in a participant subject to the intervention’. A severe adverse event will be defined as ‘any event requiring hospitalisation or causing an inability to carry out usual activities’. In the occurrence of any adverse or serious adverse event, the research team will report to the governing ethics committee, review relevant risk assessments, aim to mitigate future risk of adverse events and provide the appropriate duty of care to the participant/s concerned.

### Data collection, management and monitoring

The principle investigator and trained research assistants will collect all data from the study participants. Inter- and intra-tester reliability will be determined for data-collecting investigators and research assistants for all outcome measures as appropriate. Computer files containing study data will be de-identified and password protected with access only available to study investigators. Data entry will be performed in duplicate and accuracy will be assessed with automatic cross-checking procedures. Range checks for data values will be performed to promote data quality. All hard-copy data files will be stored in a securely locked filing cabinet at the School of Human Movement and Nutrition Sciences, The University of Queensland. Disposal of hard-copy files will be performed in accordance with general procedures, the regulations of the administering ethical board and The University of Queensland.

Electronic copies of participant data and audio recordings and transcripts of peer supporter interviews will be stored in various modes (computer hard drive; external hard drive; and cloud-based systems) all of which will be de-identified and password protected, maintaining confidentiality at all times. Electronic data repositories will only be accessible by the study investigators and associated data analysts. Results will be made available to participants (including any publications that result from the project) upon individual request following the completion of the study. Individual participants will not be identified in any resultant manuscripts or reports of this trial.

The investigators will comply with the Good Clinical Practice (GCP) guidelines adopted by the Therapeutic Goods Administration and will document and appropriately address all adverse events through Human Research Ethics Committee of Bellberry Ltd. The study investigators will permit study-related monitoring, audits, and inspections by Bellberry Ltd. of all study related documents (e.g. source documents, regulatory documents, data collection instruments, study data) and study facilities (e.g. diagnostic laboratory). An independent data monitoring committee is not needed, given the role of Bellberry Ltd. This study will be conducted in full conformance with the principles of the ‘Declaration of Helsinki’ according to international standards of GCP guidelines, applicable Australian government regulations, and Institutional research policies and procedures.

### Following study completion

On completion of a participant’s enrolment in the study, they will be offered general exercise oncology recommendations and directed to nearby community exercise programs or Accredited Exercise Physiologists for continued care.

### Statistical considerations and data analysis

A priori power calculations determined that a sample of *n* = 188 (*n* = 94 per group) will be needed to detect a minimum between-group difference in MVPA levels at 12 months, with 80% power and 5% alpha. To account for an anticipated dropout rate of 20%, 226 participants (*n* = 113 per group) will thus be recruited for this study. A priori criteria for successful provision of peer support will be contacting participants on average on one or more occasions per week over the 12-month maintenance phase.

Data will be assessed for normality of distribution using the Kolmogorov-Smirnov test. Raw continuous data (e.g. minutes of MVPA per day) will be analysed using linear mixed (fixed and random) modeling, to assess changes over time and differences between groups. Group, time, and group × time interaction will be treated as fixed factors; participants will be treated as a random factor with individual intercepts. Each model will include covariates, as appropriate, and will be adjusted using the baseline value as a fixed continuous covariate as previously described by Courneya et al. [113]. Model residuals will be formally assessed for normality by use of the Kolmogorov-Smirnov test and visual inspection of histogram plots. Bonferroni pairwise adjustments will be made for all subsequent comparisons.

Non-continuous data will be analysed with the target distribution and relationship fixed to multinomial logistic regression. Statistical significance will be set at an alpha of *p* < .05 and analyses will be conducted using the intention-to-treat approach. There are no interim analyses planned or early trial termination guidelines. Data from the peer supporters will be analysed separately to those of the participants.

Qualitative data from the semi-structured interview transcripts will be assessed using inductive thematic analysis. Codes will be assigned to salient text segments across the entire data set, before codes will be combined to define overarching themes [108].

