### Randomisation

Following completion of the 4-week supervised training phase and the second testing session, participants will be stratified by sex and age before being randomly assigned (1:1 allocation ratio) to either a peer support group or a non-peer support group. Randomisation will be performed using a computerised random number generator by a research officer independent to the study. Non-systematic block sizes of four, six, or eight will be used to ensure allocation concealment. Randomisation history will be kept secure by the independent research officer in an electronic password-protected file. The independent research officer will confidentially communicate the allocation result to the trial’s primary investigator within 48 h after completing outcome testing following the second testing session. All investigators will be blinded to group allocation for baseline testing, the supervised phase and for testing following the supervised phase, with randomisation occurring after the completion of testing following the supervised phase. The primary outcome will be analysed by a researcher blinded to group allocation. Unblinding will not be permissible under any circumstances. A schematic representation of the study protocol is shown in Fig. 1.

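### The 20% dropout allowance was multiplied on rather than divided out, so 226 participants leave about 181 at 12 months, 7 short of the 188 stated as needed

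*Protocol article*

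**What the plan says.** The section Statistical considerations and data analysis gives the requirement first: "A priori power calculations determined that a sample of *n* = 188 (*n* = 94 per group) will be needed". The purpose is "to detect a minimum between-group difference in MVPA levels at 12 months", "with 80% power and 5% alpha". The size of that difference, the SD and the sidedness of the test are not given.

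The allowance for loss follows at once: "To account for an anticipated dropout rate of 20%, 226 participants". The sentence fixes the group size as well: "226 participants (*n* = 113 per group) will thus be recruited for this study". The Abstract and the Participants section repeat 226, there as the number to be invited. Nowhere does the article give another basis for that figure.

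The Randomisation section places allocation after the supervised exercise phase: "Following completion of the 4-week supervised training phase and the second testing session, participants will be stratified by sex and age", and then "randomly assigned (1:1 allocation ratio) to either a peer support group or a non-peer support group".

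**The concern.** The requirement, the dropout rate and the target stand next to each other and do not agree. A target meant to absorb 20% loss should leave the required number once that loss has happened. Taking 20% off 226 does not leave 188.

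What is at stake is the accuracy of the primary sample-size statement. The trial recruits to 226, and a reader will take that number as protecting 80% power at 20% dropout. It does not quite do so. A fuller protocol or a separate analysis plan could not cure this, because the conflict lies between figures that the article itself prints.

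A smaller point concerns what 226 counts. It is described as the number recruited and also as 113 per group, yet groups exist only after 4 weeks of supervised training and a second test session. The article does not say whether the dropout rate covers that earlier period.

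**Working it through.** **Inputs, all from Statistical considerations and data analysis unless noted**
- Required for analysis: 188 in total, 94 per group
- Anticipated dropout: 20%
- Target: 226 in total, 113 per group
- Power 80%, alpha 5%
- Allocation 1:1 (Randomisation section)

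**Step 1. Reproduce the printed target.** Multiplying by (1 + dropout) matches both figures:
- 188 × 1.2 = 225.6, rounded to 226
- 94 × 1.2 = 112.8, rounded to 113

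**Step 2. What 226 leaves at 20% dropout.**
- 226 × (1 − 0.20) = 180.8, about 181
- 113 × 0.80 = 90.4, about 90 per group
- Shortfall: 188 − 181 = 7

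**Step 3. The number that 20% dropout implies.** Required number / (1 − dropout):
- 188 / 0.80 = 235
- With equal groups: 94 / 0.80 = 117.5, rounded up to 118 per group, 236 in total
- Gap to the printed target: 9 (235) or 10 (236). Rounding does not explain this.

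**Step 4. The dropout that 226 can absorb.**
- 1 − 188/226 = 38/226 = 16.8%

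**Step 5. Effect on power.** The 188 cannot be rebuilt, because no difference or SD is given. The standardised difference *d* was therefore solved back from 94 per group, 80% power and a two-sided 5% test of two means. The two-sided, unadjusted test is an assumption.
- Normal approximation: *d* = (1.960 + 0.842) × √(2/94) = 0.409
- *t*-test: *d* = 0.411

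| Analysed per group | Power, normal | Power, *t*-test |
|---|---|---|
| 94 | 80.0% | 80.0% |
| 90.4 | 78.4% | 78.4% |
| 90 | 78.3% | 78.3% |

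The loss at 90.4 per group is 80.0 − 78.4 = 1.6 points. The calculation counts only participants with 12-month data and makes no use of baseline or earlier visits.

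**The case against.** The strongest reply is that the shortfall has little practical effect. It is 7 participants and under 2 points of power. The planned analysis is also not the simple comparison used above: it is a linear mixed model, adjusted for the baseline value, with MVPA measured at several visits and an intention-to-treat approach. Participants lost after 3 or 6 months still contribute. If 188 came from an unadjusted formula, a baseline–outcome correlation of about 0.2 would offset the loss, since 1 − r² = 180.8/188 gives r = 0.196.

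The point about size stands. The point about the model stands only as a possibility. The correlation is not in the article, and neither is the method behind 188, which may already include adjustment. The article does not credit its 80% or its 226 to the mixed model. It states a requirement and an allowance for loss, and the allowance does not secure the requirement.

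A reader might also go further and infer that losses during the supervised phase come off the 226 on top of the full 20%, so that power falls well below 78%. The article does not support this. It gives no rate of loss before randomisation and does not say where its 20% begins. If the 20% runs from recruitment to 12 months, about 181 remain and there is no further loss to count. If 113 per group means 226 randomised, earlier losses do not come off the 226 at all. A further drop needs a third reading: 226 enrolled, with the 20% counted only after randomisation. The text does not establish that reading. What remains is an ambiguity to clear up, not an additional error.

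**Conclusion.** The concern holds as an arithmetic error in the stated target. Dropout was added to the requirement instead of divided out, so the printed 226 does not retain the 188 that the same section says is needed. This part rests on the article's own figures alone.

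The consequence is minor. The power of about 78% assumes an unadjusted, complete-case, two-sided comparison of two means, with an effect size solved back from the printed requirement. It should be quoted with that qualification. It would be wrong to infer that the trial is seriously underpowered or that the design must change.

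Whether 226 means enrolled or randomised, and what period the 20% covers, cannot be settled from the article.

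**What to change.** Correct the dropout sentence in Statistical considerations and data analysis in one of these ways:

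- Keep 226 and state that it retains 188 if dropout is at most about 16.8%.
- Keep 226 and 20% dropout, and state that about 181 are then expected at 12 months, giving about 78% power on the unadjusted basis.
- Keep 20% dropout and 80% power, and give the number these imply: 235, or 236 (118 per group) with equal arms.

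Whichever is chosen, say in the same sentence whether the number counts participants enrolled or randomised, and whether the 20% includes losses during the 4-week supervised phase. Use the same definition where 226 appears in the Abstract and the Participants section.

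The first two options cost one reworded sentence and a slightly less favourable stated figure, with no added recruitment. The third costs 9 or 10 more participants.

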**Methods:**

Men and women previously diagnosed with histologically-confirmed breast, colorectal or prostate cancer (*n* = 226), who are >1-month post-treatment, will be invited to participate in this trial. Once enrolled, participants will complete 4 weeks (12 sessions) of supervised high intensity interval training (HIIT). On completion of the supervised phase, both groups will be provided with written recommendations and verbally encouraged to achieve three HIIT sessions per week, or equivalent exercise that meets the exercise oncology guidelines. Participants will be randomly assigned to receive 12 months of peer support, or no peer support (control). Primary and secondary outcomes will be assessed at baseline, after the 4-week supervised HIIT phase and at 3-, 6- and 12-months. Primary outcomes will include accelerometry-derived MVPA and prescribed HIIT session adherence; whilst secondary outcomes will include cardiorespiratory fitness ($$ \dot{\mathrm{V}}{\mathrm{O}}_{2\mathrm{peak}} $$), body composition, quality of life and select cytokines, myokines and inflammatory markers. Random effects mixed modelling will be used to compare mean changes in outcomes between groups at each time point. A group x time interaction will be used to formally test for differences between groups (alpha =0.05); utilising intention-to-treat analyses.

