### Outcomes

Primary and secondary outcomes will be measured at baseline, at the end of the 4-week supervised phase, and at 3-, 6- and 12-months following the supervised phase. See Table 1 for a visual representation of the data collection schedule.

Assessments will be performed in a consistent order to allow for appropriate rest periods and to ensure that successive outcomes are minimally influenced by accumulative testing-fatigue. Participants will be advised to take prescribed medications as normal throughout the study period. Concomitant study participation will be documented at each testing session and the primary investigator will determine whether any co-intervention bias may influence the trial outcomes. Hospital admissions and any alterations in medical status or medications will be recorded at each assessment for future reference during analysis of results.

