### Primary outcome

#### Moderate-to-vigorous physical activity

The primary outcome for this study will be MVPA at 12 months. MVPA can be accrued through performance of the prescribed HIIT sessions and/or by engaging in any MVPA. Daily physical activity will be assessed through the use of training diaries, retrieval of HR and Wattbike ergometer data from each training session, as well as Actigraph GT3X+ accelerometry (Pensacola, Florida). Participants will be asked to wear an accelerometer on an elastic waist belt aligned with the right anterior axillary line for 7 days immediately preceding baseline, 3-, 6- and 12-month assessments. Participants will be asked to complete a brief log to record when they wear the monitor, including wake and sleep times and if they removed the monitor for > 10 min. They will be instructed to wear the device at all times, excluding sleep, any water-based activities (e.g. showering/swimming) and contact sports. Accelerometers will be initialised with 30 s epochs and a 30 Hz sampling frequency. A valid day will be defined as a minimum wear-time of 10 waking hours, with non-wear time defined as 60 min or more of consecutive activity counts of zero. For activity data to be included, participants must satisfy a minimum wear-time criterion of at least four of the 7 days, with at least one of the days being a weekend day [44, 45]. Minutes of MVPA will be calculated using Actilife v6 (Pensacola, Florida) and the cutpoints described by Troiano et al. [44].

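### The random-intercept model may give the 12-month MVPA contrast a miscalibrated standard error, too small if correlation with baseline decays; visit-specific covariance removes the risk cheaply

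*Protocol article*

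**What the plan says.** All quotes are from the protocol article.

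- **Endpoint** (Moderate-to-vigorous physical activity): "The primary outcome for this study will be MVPA at 12 months". The sample size in Statistical considerations and data analysis is set for the same time point.
- **Fixed effects** (Statistical considerations and data analysis): "Group, time, and group × time interaction will be treated as fixed factors".
- **Random effects** (same section): "participants will be treated as a random factor with individual intercepts". No random slope, other residual structure or robust standard error is named.
- **Baseline** (same section): each model "will be adjusted using the baseline value as a fixed continuous covariate". No baseline x time term is named.
- **Checks and multiplicity** (same section): residuals are checked for normality only, and later pairwise comparisons get a Bonferroni adjustment.
- **Formal test** (Abstract, Methods): "A group x time interaction will be used to formally test for differences between groups (alpha =0.05").
- **Visits**: the Outcomes section says "Primary and secondary outcomes will be measured at baseline, at the end of the 4-week supervised phase, and at 3-, 6- and 12-months", and Table 1 agrees. The accelerometry text says the device is worn "for 7 days immediately preceding baseline, 3-, 6- and 12-month assessments", which leaves out the post-supervised visit. So it is unclear whether MVPA has three or four rows after baseline.

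**The concern.** A participant random intercept with one residual variance implies equal variance at every visit and equal correlation between every pair of visits. The single baseline slope is likewise shared by all visits.

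Repeated measures often correlate less with baseline as time passes. If that happens here, adjustment removes less variance at 12 months than at 3 months, even when the raw SDs are equal. The model then applies an average variance to the visit where the true one is largest. The primary estimate would carry a confidence interval that is too narrow, and the planned normality check would not show it.

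**Working it through.** **The plan's own figure.** The article states no standard error, SD or correlation, so there is nothing of that kind to reproduce. The nearest figure is 188 evaluable participants (94 per group): "will be needed to detect a minimum between-group difference in MVPA levels at 12 months, with 80% power and 5% alpha". No difference or SD accompanies it. Backwards, 2 × (1.96 + 0.842)² / 0.41² = 93.4, so 94 per group corresponds to a standardised difference of about 0.41.

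**Formulas** (large sample, balanced data, no true effect). Let ρ_t be the correlation of visit t with baseline and s_t the SD at visit t, with baseline SD = 1.
- Common slope: b = mean of ρ_t s_t.
- Variance left at visit t: v_t = s_t² − 2bρ_t s_t + b².
- Variance the model uses at every visit: v̄ = mean of v_t.
- Ratio of model SE to true SE at 12 months: k = √(v̄ / v_12).
- Unadjusted two-sided type I error: 2 × (1 − Φ(1.96k)). Coverage of a nominal 95% interval is one minus this.

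All values of ρ and s below are assumed. Visits are 3, 6 and 12 months.

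**Worked example: ρ = 0.7/0.6/0.5, equal SDs.**
- b = 0.6
- v = 1 − 1.2ρ + 0.36 = 0.52, 0.64, 0.76; v̄ = 0.64
- k = √(0.64/0.76) = 0.918
- Type I error 7.2%, coverage 92.8%

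**Range**

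| Assumed ρ at 3/6/12 months | Assumed SDs | k | Type I error |
|---|---|---|---|
| 0.7/0.7/0.7 | equal | 1.00 | 5.0% |
| 0.77/0.75/0.70 | equal | 0.945 | 6.4% |
| 0.71/0.65/0.54 | equal | 0.915 | 7.3% |
| 0.65/0.56/0.42 | equal | 0.913 | 7.3% |
| 0.7/0.6/0.5 | 1.0/1.1/1.2 | 0.854 | 9.4% |
| 0.7/0.6/0.5 | 1.0/0.95/0.85 | 0.995 | 5.1% |
| 0.7/0.7/0.7 | 1.0/0.95/0.85 | 1.10 | 3.1% |

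The last row: b = 0.653, v = 0.512, 0.460, 0.372, v̄ = 0.448, k = √(0.448/0.372) = 1.10, so the SE is too large.

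**Post-supervised visit as a fourth outcome row.** Extending the three decaying equal-SD cases in the table back to that visit makes the SE 8-14% too small, with type I error 7.0-9.0%.

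**Simulation check.** REML random-intercept fits, 2,000 trials per case and 94 per arm, gave SE ratios of 0.90 and 0.90 (type I error 7.3% and 7.5%) for ρ = 0.71/0.65/0.54 and 0.65/0.56/0.42 with equal SDs. With 113 per arm and 20% progressive dropout they gave 0.92 and 0.92 (7.2% and 7.5%). With constant correlation 0.7 they gave 0.98 (4.6%).

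**Interaction test.** In separate simulations over assumed decay and SD patterns, the overall group x time F-test rejected 4.9-5.8% of the time under no effect.

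**Bonferroni.** If it covers three visit contrasts, the threshold is 0.05/3 = 1.67% (critical value 2.394). In the worked example the contrast then rejects 2 × (1 − Φ(2.394 × 0.918)) = 2.8% of the time. That is above the nominal 1.67% but below 5%. The SE and any unadjusted interval do not change.

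**The case against.** There are four serious objections.

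1. **Nothing in the article shows that the residual variance grows.** A reader might infer that baseline adjustment itself makes it grow and that the 12-month SE is therefore too small. The document does not support this. Falling correlation with baseline or rising SDs are needed as well, and no SD or correlation is given for any visit. The Background's remarks on reduced activity after interventions describe lower participation, not participants growing apart. MVPA cannot fall below zero, so a lower mean could shrink the SD, which weakens or reverses the effect. This objection stands and makes the point conditional.

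2. **The formal test is the interaction.** A reader might infer that the trial's false-positive rate exceeds 5%. The named test holds close to 5%, and Bonferroni, if it covers the visit contrasts, can bring the contrast below 5%. Its scope is not spelled out. This too stands. However, the interaction asks whether the group difference changes between visits. It does not supply the 12-month estimate and interval that the primary outcome calls for.

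3. **Covariance detail belongs in an analysis plan.** A random intercept can be combined with visit-specific residual variances, and an unseen plan may do that. So the pooled variance is the usual default rather than something the article states. Yet the article does not stay silent on the structure: it names a random intercept, one baseline covariate and a normality check. The choice it states can fairly be reviewed.

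4. **The model is common and the effect modest.** True for level SDs. The alternative is a better choice rather than the repair of a plain mistake.

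**Conclusion.** The point holds conditionally. As worded, and with the usual single residual variance, the 12-month contrast gets a variance pooled over visits, and its SE is right only if the residual variance at 12 months equals that average.

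- **Correlation with baseline decays, SDs level:** SE about 5-9% too small, unadjusted type I error about 6-7%.
- **SDs also rise, or the post-supervised visit is an outcome row:** larger; about 15% too small in the rising-SD example and up to 14% in the four-row cases.
- **Constant correlation, equal SDs:** correct.
- **SDs fall:** correct, or too large by up to about 10% in the cases examined; a small fall need not fully offset the decay.

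Every size rests on assumed correlations and SDs. What survives is a possibly miscalibrated standard error and confidence interval for the primary endpoint. A definite excess of false positives in the trial is not shown. A change is worth making because the remedy works in either direction and costs little.

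**What to change.** Before unblinded analysis, change the primary model as follows:

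- Use the 3-, 6- and 12-month visits as outcome rows. The post-supervised assessment precedes randomisation and should not be one.
- Replace the random intercept with an unstructured covariance over these three visits (3 variances and 3 covariances, so 6 parameters).
- Add a baseline x visit term so that the baseline slope can differ by visit.
- Fit by REML with Kenward-Roger degrees of freedom.
- Take the 12-month group contrast and its confidence interval from this model.
- Name heterogeneous Toeplitz as the fallback if the model does not converge.

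**Cost:** revised wording and a few more parameters, affordable with about 180 evaluable participants (226 × 0.8 = 181). No new data are needed. The 12-month interval may be slightly wider. If the random intercept would have been adequate, little is lost.

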### Peer support intervention

Participants randomised to the peer support group will be assigned a peer supporter. Assignment will be determined by training time availability and preference to enhance the ease of scheduling face-to-face exercise sessions. The peer supporter will maintain weekly contact (by phone, email and/or joining training sessions) with their participant for the 12-month maintenance phase. Contact frequency and type will be diarised by the peer supporter following each occurrence. The peer supporter’s goal will be to encourage their participant to maintain physical activity levels throughout the 12-month training period, equivalent to those achieved during the supervised phase. Peer supporters will be encouraged to use the knowledge and strategies gained from the CCQ peer support training sessions during discussions with their participants i.e. goal setting and planning, facilitating self-efficacy, improving confidence, overcoming barriers and building motivation. Where peer supporters have difficulty maintaining the recommended weekly contact regime, they will be encouraged to notify the research team to discuss and apply appropriate strategies moving forward. Participants will be required to diarise each exercise training session. Cycle ergometers will record each exercise session and data will be periodically retrieved by the researcher team. The training diaries and cycle ergometer data, in conjunction with the accelerometer data, will be used to assess maintenance to physical activity and the prescribed exercise over the 12 months.

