#### Physical activity preferences

The physical activity preference questionnaire will be used to assess the physical activity context preferred by participants throughout the duration of the trial due to its potential role as a covariate [109]. The questionnaire assesses physical activity preferences for 14 contexts of format (e.g. vigorous), location (e.g. outdoors), and social setting (e.g. done alone). Participants will be asked to provide ratings that reflect their agreement with one of two bi-polar statements at each end of the continuum (e.g. ‘Strongly disagree’ – ‘Strongly agree’) [110].

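### The written model does not name the stratification factors, has no supporter term if peers are shared, and does not limit covariates to values measured before randomisation

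*Protocol article*

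**What the plan says.** All statements are from the Protocol article.

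- **Fixed part** (Statistical considerations and data analysis): group, time, group × time and the baseline value of the outcome. The sentence that adds the baseline value opens with "Each model will include covariates, as appropriate". It gives no list and no rule on when a covariate must have been measured.
- **Random part** (same section): "participants will be treated as a random factor with individual intercepts". No other random term is given.
- **Strata** (Randomisation): "participants will be stratified by sex and age before being randomly assigned (1:1 allocation ratio". The age bands are not given. Randomisation follows the testing at the end of the supervised phase (Post-SP).
- **Supporters** (Peer support intervention): "Participants randomised to the peer support group will be assigned a peer supporter", matched on training times and preference. The number of participants per supporter is not stated.
- **A candidate covariate** (Physical activity preferences): the context that participants prefer is assessed "throughout the duration of the trial due to its potential role as a covariate". Table 1 schedules this questionnaire at Pre-SP, Post-SP, 3, 6 and 12 months.

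**The concern.** An analysis should follow the design that produced the data. Three features of this design have no firm counterpart in the written model.

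1. **Strata.** Stratified randomisation balances the arms on sex and age. A model without those factors still reports a standard error as if the balance were due to chance, so the standard error is too wide.
2. **Supporters.** Participants who share a supporter share that person's skill and contact habits. Their outcomes would then be correlated in the peer arm only. A model with participant intercepts alone would give too narrow a standard error, which favours a false claim of benefit.
3. **Covariate timing.** The preference questionnaire includes social setting, such as exercising alone. A supporter who joins sessions could change that answer. Adjusting for a 3-, 6- or 12-month value could remove part of the effect that the trial is meant to estimate.

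The first two act on the standard error in opposite directions. They depend on unrelated quantities, so they cannot be assumed to cancel.

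**Working it through.** **Inputs from the plan.** 188 evaluable participants, 94 per group, "with 80% power and 5% alpha". Sidedness is not stated; I assume two-sided. The section says that this number "will be needed to detect a minimum between-group difference in MVPA levels at 12 months" but gives neither the difference nor its SD, so 188 cannot be reproduced forwards. Solved backwards with the normal approximation:

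d = (1.960 + 0.842) × √(2/94) = 2.802 × 0.1459 = 0.409

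The expected test statistic is therefore 2.802, and power is Φ(2.802 − 1.960) = 80%. All figures below start there.

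**1. Strata omitted.** Let R² be the share of variance, after baseline adjustment, that the strata explain (assumption: 5-10%). The true standard error is √(1 − R²) times the one reported.

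- Type I error = 2Φ(−1.960/√(1 − R²)). R² = 0.05: 2Φ(−2.011) = 4.4%. R² = 0.10: 2Φ(−2.066) = 3.9%.
- Power without the strata = Φ(0.842/√(1 − R²)) = 80.6% and 81.3%.
- Power with the strata = Φ(2.802/√(1 − R²) − 1.960) = 82.0% and 84.0%.

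A simulation (188 participants, four strata, blocks of 4, 6 and 8, 4,000 replicates) agrees in direction. Type I error without strata was 4.8% and 3.7%, with simulation error of about 0.3 points. Power was 79.7% without against 80.7% with the strata at R² = 0.05, and 82.6% against 85.1% at R² = 0.10.

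If 5-10% is instead the share of total variance at both baseline and 12 months, and baseline correlates ρ = 0.5-0.7 with 12 months (assumption), the share left after baseline adjustment is R²(1 − ρ)/[(1 − R²)(1 + ρ)].

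- Smallest: 0.05 × 0.3/(0.95 × 1.7) = 0.9%.
- Largest: 0.10 × 0.5/(0.90 × 1.5) = 3.7%.
- Type I error is then 4.9% to 4.6%, and adjusted power 80.4% to 81.5%.

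**2. Shared supporters.** Let m be participants per supporter and ICC the intraclass correlation; neither is in the article. Only the peer arm is clustered, so the variance ratio against independence is V = (1 + [1 + (m − 1)ICC])/2. Type I error if sharing is ignored is 2Φ(−1.960/√V). Power with the correct standard error is Φ(2.802/√V − 1.960).

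| m | ICC | Peer-arm design effect | V | Type I error if ignored | Power |
|---|---|---|---|---|---|
| 1 | any | 1.00 | 1.000 | 5.0% | 80.0% |
| 2 | 0.02 | 1.02 | 1.010 | 5.1% | 79.6% |
| 4 | 0.05 | 1.15 | 1.075 | 5.9% | 77.1% |
| 6 | 0.10 | 1.50 | 1.250 | 8.0% | 70.7% |

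**3. Covariate timing.** No arithmetic is possible; the sections have to be read together. The covariate sentence sets no time limit. The preferences section proposes a scale collected throughout the trial. Table 1 gives it five visits, and the Randomisation section places allocation after the second. So Pre-SP and Post-SP values are sound covariates, while the 3-, 6- and 12-month values could be affected by the intervention. The text does not say which would be used.

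**The case against.** The strongest reply is that little here is actually wrong. The open covariate clause can hold sex and age, and a condensed article may leave the list to the full protocol or analysis plan, neither of which is shown. That stands: the strata are unnamed, not excluded. It would be wrong to infer that the model rules them out or that the group effect is biased without them. The loss is small and conservative, and smaller still once baseline activity is in the model.

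On supporters, no section says that one serves several participants. The Peer support intervention section and the training section both refer to a supporter's participant in the singular. A reader might infer that the standard error is definitely too narrow; the article does not support that, and at one participant each the effect is nil. But the article sets no limit either. Strict pairing would need up to 113 supporters, each completing the training course and the four-week supervised phase, and no supporter number is given. Sharing therefore remains possible, and the random part, which the article states outright, could not accommodate it.

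On covariates, no section commits the primary model to follow-up preferences, and legitimate earlier values exist. To say that the plan will adjust for post-randomisation variables goes too far. What remains is that the wording permits it and that a repeatedly measured candidate is named.

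**Conclusion.** The point holds as a tightening of the written model, not as proof that the result would be invalid.

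- **Strata:** no bias; type I error about 3.9-4.4% if the strata explain 5-10% of the variance left after baseline adjustment, and about 4.6-4.9% if baseline activity absorbs much of that.
- **Supporters:** conditional on sharing. Over an assumed 2-6 participants each and ICC 0.02-0.10, ignoring it gives a true type I error of about 5.1-8.0%, and power is about 80-71%. There is no effect without sharing. This is the one standard-error problem that could favour a false positive.
- **Covariates:** adjusting for follow-up preferences could remove part of the peer support effect; its size cannot be computed from the document.

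The numbers rest on the back-solved d of 0.409, two-sided testing, the normal approximation and the stated assumptions on R², caseload and ICC. The change is worth making because it is nearly free and removes discretion over the primary model.

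**What to change.** - Include sex and age, in the form used for stratification, as fixed effects in every model of a trial outcome.
- Limit covariates to values measured at Pre-SP or Post-SP, before randomisation. Preferences at later visits can be described as outcomes but not adjusted for when estimating the group effect.
- State the number of participants per supporter and keep the supporter identifier in the analysis dataset.
- If any supporter serves more than one participant, add a supporter random effect in the peer arm only (a partially nested model) with small-sample degrees of freedom. If every supporter has one participant, no supporter term is needed.

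The cost is a few sentences of analysis text and one retained variable. The downside is a few degrees of freedom and, if clustering is present, a slightly wider interval.
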